**Abstract:**

A 2-arm randomized pilot trial aimed at evaluating the effectiveness of a 6-month remote monitoring program for the management of hypertension (HTN). 300 eligible patients will be randomized in a 1:1 ratio into two recruitment arms: A) Control (usual care), or B) Remote monitoring via automated messaging program. The target population are patients at the Penn Family Medicine University City, Penn Presby and Westtown primary care practices with baseline poor blood pressure control as indicated by two blood pressures greater than 140/90 within the past twelve month including the most recent measurement and on at least one anti-hypertensive agent.

**OBJECTIVES:**

To examine the effectiveness of the chatbot supported remote monitoring program (intervention) versus usual care (control) on blood pressure control among primary care patients with poorly controlled hypertension.

Hypothesis 1a: The intervention arm will see a greater reduction in systolic blood pressure than the control arm.

Hypothesis 1b: A greater proportion of patients in the intervention arm will have well controlled blood pressure than those in the control arm.

**BACKGROUND:**

Hypertension is the world’s most common risk factor for atherosclerotic cardiovascular disease and is a leading cause of disability-adjusted life-years.1 In the US, hypertension affects 29% of all adults and 63% of older adults.2 Unlike many other diseases, safe, effective, inexpensive, and evidence-based treatments are widely available for hypertension. The implementation of these treatments is often limited by a reliance on conventional face-to-face appointments, which is ineffective as the sole basis of a population health strategy.3

One promising approach to augment face to face visits has centered on using remote monitoring supported by bidirectional text messaging. A text message supported approach has shown improved engagement, with patients more likely to measure and submit blood pressures, than other modes of outreach.4,5 At the same time, a relatively frictionless communication channel presents a conundrum for providers: frequent communication regarding blood pressure monitoring can result in better outcomes but also create more work.

A chatbot with natural language processing (NLP) capability could solve the workload challenges of bidirectional texting while facilitating engagement. We have developed a chatbot and piloted it in the Penn employee hypertension management program, demonstrating both acceptability and feasibility**.** The goal of this study is to test the program’s effectiveness in a pragmatic randomized controlled trial among primary care patients with hypertension, including in a West/Southwest Philadelphia lower SES population.

**CHARACTERISTICS OF THE STUDY POPULATION:**

***1. Target Population and Accrual:***

Patients of the primary care practices listed below who have baseline poor blood pressure control will be reached out to for this study. The study will be conducted among patients seen by Penn Primary Care Providers (PCP).

Participants in this study will be identified via electronic medical records review by our study staff. The study staff will work with UPHS to create a filter for the electronic medical record system that will generate a list of patients who may meet the study criteria. A study coordinator will review the list of patients to determine eligibility. If patients meet the study requirements, they will be included on a list that will be sent to their primary care provider for review. PCPs will have the opportunity to opt any patients out of study enrollment. Patients who are not opted out by their PCP will be randomized and recruited according to study arm.

***2. Key Inclusion Criteria:***

1) Two blood pressures > 140/90 within the past 12 months, including the most recent measurement

AND

2) On at least one anti-hypertensive agent

AND

3) On HTN registry

AND

4)On PCSL registry

5) Are active patients at the Penn Family Medicine University City, Penn Presby and Westtown pratices

***3. Key Exclusion Criteria:***

Any patients meeting the following criteria are excluded from the study:

- On a PCSK9 inhibitor medication
- Pregnant or currently breastfeeding
- Have a significant disability or markedly shortened life expectancy (metastatic cancer, on hospice, ESRD, dementia, end stage renal failure, congestive heart failure)
- Not fluent in English

*.*

***4. Subject Recruitment and Screening:***

Patients are identified through an Epic Clarity report which is run as needed, until enrollment is completed. This patient list is based on the eligibility criteria. This report will be sent to the research team.

The Research team will send PCPs a list of their patients that are being considered for enrollment through Epic in-basket messages. They will be given the opportunity to identify patients who should not be enrolled.

The patients that are not opted-out by their PCP will then be randomized to the intervention or control arm.

The message sent to the PCP can be found in the attached Patient and Provider Materials document.

## *5. Early Withdrawal of Subjects:*

The participants enrolled into the intervention will be free to opt-out at any time (they can do so by texting in “bye” or “stop”). Instructions on how to do so will be clearly stated in the introductory message. The PI may withdrawal a subject if it deemed the participant is no longer an appropriate fit for the study.

***6. Vulnerable Populations:***

No vulnerable populations are specifically included or excluded in the research study. We will include all eligible patients.

***7. Populations vulnerable to undue influence or coercion:***

We are not specifically targeting any vulnerable populations.

**STUDY DESIGN:**

Pragmatic, non-blinded, randomized controlled trial.

Randomization and enrollment:

- Randomization will be at the patient level (stratified/balanced randomization by PCP)
- Enrollment will take place over short time period based off of lists of eligible patients pulled from the EMR
- Lists of eligible patients sent to PCPs with opportunity to opt patients out. Patients will be contacted via text followed by phone call to introduce them to the program.

We expect recruitment to take approximately 1 month to reach a target sample size of 300. The program itself will be 6 months from the date of randomization. Total study duration should be approximately 7 months. Data analyses will take an additional 3 months.

The control group will receive usual care as determined by PCP (control arm will not receive BP cuffs).The Intervention Group will receive the BP cuff and weekly SMS messages asking for the BP reading. The methods section below will outline the details for both groups.

**METHODS:**

***1. Study Instruments:***

The study instrument comprises of a 6-month study visit to measure blood pressure at the conclusion of the study period and the data that is collected by Way to Health.

## *2. Group Modifications:*

Patients in the usual care arm will not be contacted by study staff at the start of the pilot, they will not receive a blood pressure cuff, and they will not receive any text messaging or any component of the program. They will eventually be contacted by study staff to schedule the 6 month BP check. Patients assigned to intervention arm will a text message notifying them of enrollment, be mailed a BP cuff and receive a recruitment phone call if nonresponsive to text. If the patient does not opt out, the research coordinator will mail a blood pressure cuff and proper measurement instructions and start their remote monitoring program in the Way to Health platform. Usual care for hypertension is as needed determined by the clinical expertise of the primary care provider and can include regular follow-up visits (in person or virtual), home blood pressure readings, titration of medications during visits or via telephone, referral to specialty care (e.g., Nephrology or Cardiology), blood tests or imaging studies.  Both arms will continue to receive usual care as directed by PCP. Therefore, there are no risks related to foregoing usual care in the intervention arm or in usual care.

*3. Method for Assigning Subjects to Groups:*

Once participants are eligible to begin the study, they will be randomly assigned to the remote monitoring program or usual care. Allocation will be 1:1. The randomization will be at the patient level and stratified by PCP.

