***Analysis of the Primary Efficacy Endpoint(s)***

The primary analysis will be an intention to treat analysis among those that met inclusion criteria and were randomized to the intervention or control arm. The primary endpoint will be a continuous measure of change in blood pressure from baseline to the 6 month study visit. Crude between group differences will be assessed using t-tests. We will also use a linear regression model. While randomization should create balance between arms, if there is any residual imbalance in covariates deemed to be associated with the outcome, these will be adjusted for to enhance efficiency. These may include: age, sex, race, ethnicity, payor group, Charlson comorbidity index. Patients enrolled in the intervention arm will be included in the analysis even if they opt out of the texting intervention (intention-to-treat). In addition, we will conduct a secondary per-protocol analysis including only those patients randomized to the intervention who completed enrollment, and ultimately received equipment and messages.

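### Randomisation is stratified by PCP, but no planned analysis names PCP and the imbalance rule for covariates would tend to leave it out; the cost is a small loss of efficiency

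*Protocol*

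**What the plan says.** The Study Design section describes patient-level allocation with "stratified/balanced randomization by PCP". Item 3 of Methods (Method for Assigning Subjects to Groups) repeats this: "Allocation will be 1:1" and "The randomization will be at the patient level and stratified by PCP". PCP is the only stratification factor named.

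The section on the primary efficacy endpoint plans two analyses of blood pressure change: "Crude between group differences will be assessed using t-tests" and "We will also use a linear regression model". Its rule for adding covariates to the regression is that "if there is any residual imbalance in covariates deemed to be associated with the outcome, these will be adjusted for to enhance efficiency". The candidates follow: "These may include: age, sex, race, ethnicity, payor group, Charlson comorbidity index". All six are patient characteristics; PCP is not among them.

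The section on secondary endpoints carries the same approach to the other continuous measures. For blood pressure control it plans a chi-squared test and a logistic regression with the same covariates. PCP appears in none of these analyses.

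**The concern.** When allocation is balanced within a factor that predicts the outcome, the true sampling variance of the treatment difference falls. An analysis that omits the factor still counts the between-stratum variance as noise, so its standard error is larger than the true one. The test is then conservative and the interval wider than it need be.

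PCP could plausibly be such a factor, because the protocol leaves hypertension care in both arms to the PCP's judgement.

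This is more than a detail left open, because the protocol fixes a rule that works against its own design. Adjustment is triggered by observed imbalance, and stratification exists to prevent that imbalance in PCP. The stated aim of adjusting is efficiency, but efficiency comes from a covariate's prognostic strength and not from its chance imbalance. For the one factor the design balances, the rule defeats its purpose.

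**Working it through.** **Inputs from the protocol.** Difference 7 mmHg, SD 17, two-sided alpha 0.05, power 80%, about 200 evaluable patients, 300 randomised (Sample Size Determination; General Approach). Up to 100/300 = one third may therefore be lost.

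**Inputs assumed.** The number of PCPs and the ICC of the outcome within PCP are not in the protocol. ICC is varied from 0 to 0.20. The SD of 17 is applied to the analysed outcome.

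**The plan's own figure.** n per arm = 2(1.960 + 0.842)² × 17² / 7² = 92.6, so 93 per arm and 186 in total. The exact t-test needs 94 per arm, 188 in total. The protocol's figure of about 200 is slightly higher, in the safe direction; 100 per arm gives 82.9% power (normal) or 82.6% (t-test).

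**Effect of omitting PCP, complete data, balanced within PCP.**

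- Reported SE without PCP = 17 × √(2/100) = 2.404.
- True SE = 2.404 × √(1 − ICC).
- Ratio of reported to true SE = 1/√(1 − ICC).
- Actual type I error of the t-test = 2[1 − Φ(1.96 × ratio)].
- Power of the t-test = Φ((7 − 1.96 × 2.404)/true SE).
- Power with PCP in the model = Φ(7/true SE − 1.96).

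| ICC (assumed) | True SE | Reported/true SE | Type I error, t-test | Power, t-test | Power, PCP in model |
|---|---|---|---|---|---|
| 0 | 2.404 | 1.000 | 5.0% | 82.9% | 82.9% |
| 0.02 | 2.380 | 1.010 | 4.8% | 83.2% | 83.7% |
| 0.05 | 2.343 | 1.026 | 4.4% | 83.6% | 84.8% |
| 0.10 | 2.281 | 1.054 | 3.9% | 84.2% | 86.6% |
| 0.20 | 2.150 | 1.118 | 2.8% | 85.6% | 90.2% |

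The t-test's own power rises with ICC, from 82.9% to 84.2% at ICC 0.10. That is the benefit of stratification reaching the estimate even when the analysis omits PCP.

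**Simulation under the same ideal conditions** (200 patients, 20 or 50 equal PCPs, 8,000 runs per setting, t-test against PCP fixed effects). At ICC 0.05 the mean SE is 2.40 against 2.34, type I error 4.3–4.6% against 4.9–5.1%, and power about 83% against 84%. At ICC 0.10 the mean SE is about 2.40 against 2.28, and power about 84% against 86%. At ICC 0 the two methods agree.

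**At 5 mmHg**, the difference named in Statistical Hypotheses, a simulation with 20 PCPs of 10 patients each (4,000 runs per ICC) gave power of 53.8% against 55.5% at ICC 0.05, and 56.1% against 59.8% at ICC 0.10.

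**Simulation with loss and uneven panels** (300 randomised, one third lost at random, 7 mmHg, 20 to 80 PCPs).

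- PCP fixed effects at ICC 0.05, t-test against fixed effects (2,000 runs per setting): 82.6% against 83.0% with 20 PCPs, 83.7% against 79.8% with 50, and 82.4% against 75.9% with 80. Dummies lose power when PCPs are many and small.
- PCP random intercept, ICC 0 to 0.10: power 82–87%, against 81–85% for the t-test. The gain was about 0 to 2 points across settings, with type I error near 5%.

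**The case against.** Four objections deserve an answer.

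1. **Handling of stratification factors is often left to the SAP, and the covariate list is introduced as what may be included.** It is true that nothing bars PCP and that a SAP not shown here could add it. What stands against this is the imbalance trigger, which is fixed in the protocol and points the wrong way for a factor balanced by design.

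2. **No between-PCP variance is documented, and the primary endpoint is a change from baseline, so stable differences in blood pressure level between PCPs largely cancel.** This stands. The effect is conditional on PCP predicting change, and the ICC may be near zero.

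3. **Adjusting for PCP can cost power.** This stands for PCP dummies with many small panels, as the last simulation shows. It does not carry over to a random intercept.

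4. **The planned power is met anyway.** This stands: 200 evaluable patients give 82.6–82.9% before any allowance for PCP.

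A reader might go further and infer that the standard errors are bound to be too large, or that the balance from stratifying is thrown away. The documents support neither. With no PCP effect there is no inflation. With one, the point estimate is still protected from PCP imbalance and its true variance still falls; only the reported SE, interval and p-value fail to show it. Nor does correlation of outcomes within PCP make this test anti-conservative, because allocation is by patient within PCP and not by PCP.

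**Conclusion.** The point holds as a minor matter of efficiency. PCP is the stratification factor, no analysis names it, and the rule for choosing covariates would tend to exclude it. If PCP predicts blood pressure change, inference will be somewhat conservative: SE about 0–5% too large for ICC 0–0.10, and roughly 0–2 points of power forgone at 7 mmHg (2.4 under ideal balance at ICC 0.10). The gain would be larger at ICC 0.20, but nothing in the protocol indicates a value that high.

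These sizes rest on an assumed ICC and number of PCPs, on the protocol's SD of 17 and, in the simulations with loss, on loss at random. Neither the validity of the test nor the planned 80% power is threatened.

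**What to change.** Add to the analysis of the primary endpoint, and carry over to the secondary continuous endpoints, a sentence such as: *The linear models will include PCP, the stratification factor, as a random intercept, irrespective of any observed imbalance.* PCP dummies should be avoided unless every PCP contributes a reasonable number of evaluable patients.

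For blood pressure control, account for PCP as well, and state that a random-intercept logistic model gives an odds ratio conditional on PCP, which differs in meaning from the marginal odds ratio of a model without PCP.

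The cost is a sentence or two, fixed before outcomes are seen. No extra patients or data are needed, since the PCP of each patient must be known in order to stratify.

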## *4. Administration of Surveys and/or Process:*

## Control Group

## 6 month in person clinic visit

## Intervention Group

## Communication via W2H

## 6 month in person clinic visit

##

## *5. Data Management:*

Data on physicians and patients will be obtained from the Epic instance and Epic’s reporting database Clarity at Penn Medicine. Any information that is obtained will be used for research purposes only. Information on patients will only be disclosed within the study team and to the patient’s primary care physician.. All study staff will be reminded of the confidential nature of the data collected and contained in these databases. To ensure that patient confidentiality is preserved, individual identifiers (such as name and medical record number) are stored in a single password protected system that is accessible to study research, analysis and IT staff only. This system, Way to Health (W2H) is hosted on site at UPenn and is protected by a secure firewall. Once a participant is in this system, they will be given a unique study identification number (ID). The study ID will also be used on all analytical files. Please see link for full W2H privacy and security details: <https://policy.waytohealth.org/>. The blood pressure data sent by participants through W2H will be transmitted via cellular signal to W2H without any subject identifiers. Penn Medicine Academic Computing Services (PMACS) will be the hub for the hardware and database infrastructure that will support the project and where the W2H project web portal is based. PMACS is a joint effort of the University of Pennsylvania's Abramson Cancer Center, the Cardiovascular Institute, the Department of Pathology, and the Leonard Davis Institute. PMACS provides a secure computing environment for a large volume of highly sensitive data, including clinical, genetic, socioeconomic, and financial information. Among the IT projects currently managed by PMACS are: (1) the capture and organization of complex, longitudinal clinical data via web and clinical applications portals from cancer patients enrolled in clinical trials; (2) the integration of genetic array databases and clinical data obtained from patients with cardiovascular disease; (3) computational biology and cytometry database management and analyses; (4) economic and health policy research using Medicare claims from over 40 million Medicare beneficiaries. PMACS requires all users of data or applications on PMACS servers to complete a PMACS-hosted cybersecurity awareness course annually, which stresses federal data security policies under data use agreements with the university. Curriculum includes HIPAA training and covers secure data transfer, passwords, computer security habits and knowledge of what constitutes misuse or inappropriate use of the server.

## STUDY PROCEDURES:

***1. Detailed Description:***

For the intervention arm, after the PCP has had the opportunity to opt out any patients they deem inappropriate, the research team will create encounters in Penn Chart and upload the list to Way To Health including the MRN and CSN. Way To Health will start enrollment for intervention patients and send introduction via text messages. The patient outreach text can be found in patient outreach document.

On a rolling basis as patients’ complete orientation, the research team will mail BP cuffs. For patients who do not complete the text message orientation, the research team will call the patients up to two times. The first phone call will be three business days after the initial outreach and the second call will be seven business days after the initial outreach. If there is no response, the patient will be deemed as “do not contact” and the research team will change their status to inactive in Way To Health.

For patients who get started in the program Way To Health will change their status to “active”. The BP reminder will begin when patients text in “READY”. The notifications will be sent to the research team when the patient starts, and the research team will update Penn Chart with documentation. If the patient does not text back “READY” then the research team will call the intervention patient up to two times, the first being 10 days after mailing and the second being 14 days after mailing

For enrollment documentation when the patient texts “READY” or confirms readiness by phone call a telephone encounter will be created to document patient enrollment. The PCP will then be able to continue to manage their patient as they normally would. Any encounters resulting from interactions via the remote monitoring program will be routed to the PCP inbox. The research team will notify the PCP of any medication changes. If the patient opts out after starting, a telephone encounter will be created, and the research team will be notified and will notify the PCP.

The BP request messaging is in the Patient and Provider materials document that is attached and will be sent weekly on the specified day and time that the patient indicated in the enrollment survey.

The BP Logic categorization is in the below table. Further information on the logic and messaging can be found in the attached Patient and Provider materials document.
[figure not shown]

[figure not shown]

[figure not shown]

For completion the of the project. Participants will be notified via text. An example of the text can be found in the attached Patient and Provider materials document.

For participant completion the research team will be notified via email. Way To Health will move patient status to finished. The patient will no longer receive texts.

**The research team uses Omni to aggregate the data on the participants. Omni**is a Penn Medicine approved, web-based platform that aggregates information from Way to Health and PennChart (electronic health record) into customizable dashboards that allow users to view information relevant to specific clinical populations. Omni’s use of real-time and retrospective data makes it a scalable platform on which new rules for individual and population-level interventions can be developed, tested, and deployed.

The research team will reach out to the PCPs upon the completion of participants. Example of how PCP will be messaged can be found in attached document of patient messaging.

If participants do not respond to the request for blood pressure three times in a row, then unresponsive logic will set in.

The initial unresponsive text they will receive can be found in the attached document of patient messaging.

The workflow based on unresponsive logic is as follows.

[figure not shown]

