**Sample Size Determination**

**We aim to power our study to detect a mean systolic blood pressure difference of 7 mmHg between study arms at the 6 months study visit. From baseline pilot data we expect a standard deviation around 17. With 80% power and a Type I error rate of 0.05, we estimate that we will need data on about 200 patients to be able to reject the null hypothesis of no difference between groups. Recognizing that there will be a reasonable rate of loss to follow-up, we plan to randomize 300 patients.**

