**Statistical Analyses**

***General Approach***

For descriptive statistics, we will present continuous data as means with standard deviation or median with interquartile range, as appropriate. Categorical data will be presented as percentages. For inferential tests, we will use a p-value of 0.05 as the cutoff for statistical significance; tests of hypothesis will be two-tailed.

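### The no-contact status for silent intervention patients has no exemption for scheduling the 6-month visit, so the primary outcome may be lost in one arm only and the intention-to-treat analysis is left unprotected

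*Protocol*

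**What the plan says.** All locations are in the protocol.

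- **Order of events.** Target Population and Accrual, and Subject Recruitment and Screening, place randomisation after the PCP opt-out and before any contact with the patient.
- **Intervention arm.** Detailed Description (Study Procedures) allows up to two calls to a patient who has not completed text orientation. If there is still no response, the patient is "deemed as “do not contact” and the research team will change their status to inactive in Way To Health".
- **Control arm.** Group Modifications gives controls no contact at the start. It then says: "They will eventually be contacted by study staff to schedule the 6 month BP check".
- **Visit.** Administration of Surveys and/or Process lists a 6-month in-person clinic visit under both groups, without exceptions.
- **Endpoint.** Data Analysis fixes the final blood pressure as the reading from that visit. Data Collection also says that EMR data from both arms, combined with home readings, will be used to assess the primary and secondary outcomes.
- **Analysis set.** The primary analysis is intention to treat over eligible randomised patients, with this specific protection: "Patients enrolled in the intervention arm will be included in the analysis even if they opt out of the texting intervention".
- **Start of the programme.** Group Modifications says: "If the patient does not opt out, the research coordinator will mail a blood pressure cuff", and then starts the programme. Detailed Description has cuffs mailed as patients complete orientation, and makes silent patients inactive.

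**The concern.** The no-contact status is assigned after randomisation, depends on the patient's behaviour, and exists in one arm only. A coordinator who follows its plain words would not ring such a patient at six months, while a control of the same temperament would still be contacted. The primary reading would then be missing for the least engaged patients in the intervention arm, and their counterparts would remain in the control arm.

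The protocol itself treats responsiveness as prognostic. It justifies the consent waiver by arguing that people who consent behave differently from those who do not, and that this would bias the results. Losing silent patients from one arm would bring back selection of that kind after randomisation.

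The specific protection for opt-outs may not reach these patients. It speaks of patients enrolled in the intervention arm, and Detailed Description documents enrolment only once the patient confirms readiness. Patients who never respond are covered by the general intention-to-treat sentence, but no written procedure secures their outcome. A reading that was never taken cannot be recovered in the analysis.

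**Working it through.** **1. The plan's own sample size.** Inputs from Sample Size Determination and General Approach: difference 7 mmHg, SD 17, "With 80% power and a Type I error rate of 0.05", two-sided.

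n per arm = 2 × (1.960 + 0.842)² × 17² / 7² = 92.6, so 93 per arm and 186 in total. The t-test version gives 94 per arm, 188 in total. The stated figure of about 200 is therefore rounded up (power 82.9% at 100 per arm). Going from 300 randomised to 200 measured allows for one third lost, with no split by arm.

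**2. Spurious benefit with no true effect.** Neither input below is in the protocol; both are assumptions.

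- f = share of the intervention arm given the status and never measured.
- D = how much less systolic pressure falls in such patients than in reachable ones. The endpoint is change from baseline, so D is a gap in change, not in level.

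Measured intervention patients average the reachable patients' change. Measured controls average a mix with share f of the less reachable type, if that type attends as often as others. The difference is f × D.

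If the less reachable controls attend at a relative rate k, their share among measured controls is q = fk / (fk + 1 − f), and the bias falls to q × D. The table uses k = 0.5, also an assumption. The last column is the two-sided rejection rate under no effect at k = 1, with 100 controls and 100(1 − f) intervention patients measured and SE = 17 × √(1/100 + 1/[100(1 − f)]).

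| f | D (mmHg) | f × D | q × D at k = 0.5 | Rejection rate, k = 1 |
|---|---|---|---|---|
| 10% | 3 | 0.3 | 0.2 | 5.2% |
| 20% | 3 | 0.6 | 0.3 | 5.6% |
| 20% | 5 | 1.0 | 0.6 | 6.8% |
| 30% | 5 | 1.5 | 0.9 | 8.7% |
| 40% | 7 | 2.8 | 1.8 | 17.2% |
| 40% | 8 | 3.2 | 2.0 | 21.1% |

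Example, last row: q = 0.4 × 0.5 / (0.2 + 0.6) = 0.25, and 0.25 × 8 = 2.0 mmHg.

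**3. If the programme works only in patients who engage.** With 7 mmHg in engaged patients and none in silent ones, the intention-to-treat effect is 7(1 − f). The contrast among measured patients is 7 + f × D. At f = 20% and D = 5 these are 5.6 and 8.0 mmHg.

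**4. Power for 7 mmHg**, with one third lost in both arms and a further share f lost from the intervention arm:

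| f | Measured (control + intervention) | Power |
|---|---|---|
| 0 | 100 + 100 | 82.9% |
| 10% | 100 + 90 | 80.9% |
| 20% | 100 + 80 | 78.4% |
| 30% | 100 + 70 | 75.2% |
| 40% | 100 + 60 | 71.3% |

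These power figures are pessimistic. Many silent patients would have been part of the planned one-third loss anyway, so stacking the two losses counts some patients twice.

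**The case against.** The strongest reply is that the status covers the programme only. It sits in the enrolment workflow and is tied to a Way To Health setting. The 6-month visit is listed for the intervention group without exception, and Subject Privacy foresees calls to arrange the final measurement without limiting them to one arm. This reading makes the sections agree, and the sponsor may well intend it. It is not written down, however, and the no-contact label is applied in addition to the inactive setting.

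A reader might infer that silent patients are excluded from the visit. No sentence says so. A reader might also infer that intention to treat cannot be delivered. That does not follow: the visit is planned for both arms, EMR outcome data are named for both arms, and the handling of missing data may sit in a SAP that is not at hand. The EMR is only a partial remedy, because Data Analysis fixes the final value as the visit reading. Home readings through Way to Health come only from intervention patients using the programme.

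The objection to the size also stands. People who ignore texts and two calls may equally ignore a request to attend a clinic, so f × D is an upper limit. The direction is open too: patients selected for high readings who start highest may regress most, which could reverse the sign.

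Finally, it is tempting to add the withdrawal clause, "The PI may withdrawal a subject if it deemed the participant is no longer an appropriate fit for the study". It applies to a subject in either arm, and nothing says that it removes anyone from the analysis. It is relevant only because follow-up after withdrawal should be covered by the same sentence.

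**Conclusion.** The point holds as a defect of wording with consequences for the primary endpoint. A status given after randomisation, which only intervention patients can acquire, has no stated exemption for scheduling the visit that supplies the primary reading. Followed literally, it contradicts the visit schedule for both groups, risks arm-dependent loss of outcomes, and leaves the intention-to-treat analysis without a procedure behind it.

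With no true effect, the spurious benefit is at most about 0.3 to 3.2 mmHg, against a hypothesised 5 mmHg and a powered 7 mmHg. This rests on assumed f of 10–40% and D of 3–8 mmHg, and on equal attendance by similar controls. Halving their attendance brings the range to about 0.2 to 2.0 mmHg. A bias in favour of the intervention is plausible but not documented.

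The disagreement between Group Modifications and Detailed Description over when a cuff is mailed and the programme started is also real. It concerns delivery of the intervention, not measurement of the outcome, and is a separate matter.

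**What to change.** 1. In Detailed Description, state that the no-contact and inactive status applies to the remote-monitoring programme only.
2. State that all randomised patients in both arms receive the same 6-month visit scheduling attempts unless they refuse follow-up contact. Name explicitly those who never responded, those who opted out of texting and those withdrawn from the programme.
3. Separately, reconcile Group Modifications with Detailed Description on when the cuff is mailed, when the programme starts, and what happens to a patient who neither responds nor opts out.

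The cost is a few sentences of protocol text, some more scheduling calls by existing staff, and the $75 visit payment already planned for each patient who attends. The change must be in place before the 6-month visits, because a missed reading cannot be recovered afterwards.
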